## SYNOPSIS

|                              |                                                                                                                                                                                                                                                                                                                                                                                                                                                                                                                  |
|------------------------------|------------------------------------------------------------------------------------------------------------------------------------------------------------------------------------------------------------------------------------------------------------------------------------------------------------------------------------------------------------------------------------------------------------------------------------------------------------------------------------------------------------------|
| Study name            | Effect of BSE on blood glucose                                                                                                                                                                                                                                                                                                                                                                                                                                                                                   |
| Protocol number       | 3                                                                                                                                                                                                                                                                                                                                                                                                                                                                                                         |
| Study location        | Gothia Forum, [name] (Sahlgrenska University Hospital), [name], Sweden                                                                                                                                                                                                                                                                                                                                                                                                                        |
| Number of subjects    | 100                                                                                                                                                                                                                                                                                                                                                                                                                                                                                                              |
| Study design          | Randomized double-blinded parallel arm                                                                                                                                                                                                                                                                                                                                                                                                                                                                           |
| Study population      | Individuals with pre-diabetes                                                                                                                                                                                                                                                                                                                                                                                                                                                                                    |
| Aims                  | The aim of the study is to measure the effect of broccoli sprout extract (BSE) on fasting glucose                                                                                                                                                                                                                                                                                                                                                                                                                |
| Summary of study plan | Here we will investigate the effect of sulforaphane, provided as a broccoli sprout extract (BSE) on blood glucose in pre-diabetic individuals without metformin treatment. This will address whether BSE could be used to improve glucose control in drug-naïve pre-diabetic individuals. The participants will receive BSE or placebo in a randomized double-blind parallel arm study. The participants will take their study compound once daily over 12 weeks. The primary study variable is fasting glucose. |
| Duration of study     | Aug 2018- Dec 2020                                                                                                                                                                                                                                                                                                                                                                                                                                                                                               |

## 1. BACKGROUND

Type 2 diabetes (T2D) is an escalating health problem of enormous proportions. An alarming 350 million persons have T2D, and the number is expected to exceed 500 million by 2030. The disease poses a heavy burden on health care systems in both developed and developing countries. The disease leads to devastating complications in kidneys, eyes and the cardiovascular system.

T2D results from a combination of insufficient insulin secretion from pancreatic islets and insulin resistance of target cells. T2D develops slowly and there is a large number of people in the general population that are at risk for T2D. The people from the general population that have progressed farthest towards T2D are said to have ‘pre-diabetes’, defined as impaired fasting glucose or impaired glucose tolerance. Lifestyle changes, including dietary interventions, is a cornerstone to counteract the progression of prediabetes to overt T2D. However, many people find it difficult to know what to eat, because of conflicting reports, and there are many well-studied psychological reactions that make lifestyle changes difficult, including lack of motivation, loss aversion (aversion to give up established lifestyles), and automatic behaviour.

Metformin is first-in-line treatment for newly diagnosed T2D. However, 15% of all T2D patients cannot take metformin because of reduced kidney glomerular filtration rate and hence increased risk of lactic acidosis. Moreover, many patients treated with metformin develop nausea, bloating, abdominal pain, or diarrhea, and another 5 to 10% of the patients are unable to continue with metformin because of the gastrointestinal problems. This also limits the use of metformin as a long-term treatment for preventing T2D.

Clearly, new options are needed to more effectively prevent T2D. Since diet is so central, new food supplements (“functional food”) could be one potential avenue, as they may have fewer side effects and be more easily tolerated. A limitation to current functional foods is lack of understanding of the mechanism of action and insufficient scientific effect evaluation.

We have recently identified sulforaphane as a new anti-diabetic compound that counteracts exaggerated hepatic glucose production in obese T2D patients (Axelsson et al., *Science Translational Medicine*, 2017). The identification was made possible by analysing genetic and gene expression data from liver tissue to construct a ‘disease signature’ of 50 genes that are perturbed in patients with T2D. We then compiled a library of 3800 ‘drug signatures’, using publically available expression data ([www.ncbi.nlm.nih.gov/geo](http://www.ncbi.nlm.nih.gov/geo)). A drug signature represents the genes for which the expression is significantly affected by a specific compound. The drug signatures were matched with the disease signature to find compounds that could potentially reverse the aberrantly expressed disease genes (overexpressed T2D genes should be downregulated in the drug signature and vice versa).

From these analyses, sulforaphane stood out as the highest ranked compound. Sulforaphane is highly contained in broccoli sprout extract, BSE, and has previously been studied clinically for cancer prevention but has not been implicated in T2D. We first observed that the

compound suppressed glucose production from hepatic cells by nuclear translocation of the transcription factor NRF2. This led to decreased expression of key enzymes in gluconeogenesis. Next, the compound was shown to reduce gluconeogenesis and improve glucose intolerance in diabetic animals by a magnitude similar to that of metformin. The treatment also reversed the 50-gene disease signature in the liver from these animals.

Finally, we translated the findings to patients with T2D. In collaboration with Lantmännen (the Swedish farmer's association) we generated a water-soluble powder of broccoli sprout extracts (BSE) containing high concentrations of sulforaphane. In mice, BSE, provided as gavage, improved glucose tolerance to the same extent as HPLC-purified sulforaphane. Inactivation of sulforaphane in the BSE by boiling abolished the effect, demonstrating that sulforaphane is the active component in this case.

We then recruited 97 patients with T2D and metformin treatment who received BSE (with 150  $\mu$ mole sulforaphane) or placebo (randomized double-blind) once daily over 12 weeks. In obese patients ( $\text{BMI} > 30 \text{ kg/m}^2$ ) with dysregulated T2D, BSE improved HbA1c by 4 mmol/mol ( $p < 0.05$ ) and fasting glucose by 0.9 mM ( $p < 0.05$ ). The effect size is in the same range as that seen by recently approved anti-diabetic DPPIV-inhibitors. BSE had no severe adverse effects in this study, in agreement with previous studies.

## 2. RATIONALE FOR THE STUDY AND STUDY DESIGN

Here we will extend on our previous study by investigating the preventative effects of BSE with standardized amounts of sulforaphane (at least 150  $\mu$ mole daily) in pre-diabetic individuals. This will address whether BSE could be used to improve glucose control in drug-naïve pre-diabetic individuals.

BSE would be an attractive food supplement to reduce blood glucose for several reasons. 1) We have extensive data from diabetic animal models and T2D patients that BSE improves fasting glucose. 2) Hepatic glucose production is typically exaggerated in individuals at risk for T2D and it is a central pathophysiological process that leads to increased fasting glucose and progression to T2D. We have characterized the mechanism of action of sulforaphane in the BSE and shown that it affects the anti-oxidative NRF2 system, and leads to reduced expression of gluconeogenic enzymes and hence suppressed hepatic glucose production. The compound therefore counteracts a key mechanism leading to T2D. 3) Metformin, which also reduced hepatic glucose production (although via different mechanisms), has side effects that means that all people cannot tolerate metformin. BSE have few adverse effects. BSE is being tested for the treatment or prevention of cancer and inflammatory diseases in ~30 clinical trials without any serious adverse events reported. Moreover, cruciferous vegetables, including broccoli sprouts, are regular dietary components in many regions of the world. Based on the widespread use of broccoli sprouts as a food and previous human studies with BSE, including our own recent study, no severe or serious risks are anticipated to be associated with the administration of BSE. The low toxicity makes BSE ideal as a food supplement for reducing blood glucose and prevent T2D.

We aim to study the effect of BSE with standardized amounts of sulforaphane on fasting glucose in pre-diabetic individuals, here defined as having impaired fasting glucose. Based on the mechanism of action of sulforaphane, we focus on individuals with impaired fasting glucose rather than impaired glucose tolerance (i.e. elevated glucose levels after glucose ingestion). Our previous characterization of the mechanism of action also enables us to focus on the most relevant variable, in this case fasting glucose, which consequently will be the primary study variable.

BSE is a freeze-dried powder of an aqueous extract of broccoli sprouts that provides a consistent and stable source of sulforaphane. We will use a parallel arm study design with 50 subjects receiving BSE and 50 receiving placebo. The randomization will be double-blind. The study will be done at one centre. Subjects will be treated for 12 weeks.

### **3. PROJECT DESCRIPTION**

#### **3.1 Recruitment**

A random selection of members of the general population aged 35-75 years in Göteborg and surrounding municipalities, who have registered addresses and Swedish personal numbers, will receive an invitation letter with study information. The letter will be sent by regular post via PostNord. The addresses will be retrieved from the general population address registry. This is a large and socially heterogeneous area, which means that the invitation letters will reach a broad spectrum of the general population.

Interested participants go to a dedicated study website, which has a simple interface for booking a time for a screening visit. The website has the necessary IT security and the participants will not be able to see which other people have booked a time (they will only see available and non-available slots).

They enter their name, telephone number and email address. They receive a confirmation email with instructions for the screening visit.

It is not a prerequisite to have received the letter to participate, which means that people who get to know about the study through other channels (e.g. media coverage, word of mouth) will also be able to participate in the study.

It is possible to re-screen a person who at some occasion has had pre-diabetic glucose values but because of variation in fasting glucose was not included in the first assessment (screening failure at screening visit or visit 2). Anyone who is re-screened will start over again with a new written informed consent, a new screening number and the person has to pass the study criteria at both the new screening visit and visit 2 to be randomized.

#### **3.2 Study criteria**

##### **Inclusion criteria**

- Impaired fasting glucose, defined as fasting blood glucose 6.1-6.9 mM.
- Written informed consent
- Age 35-75 years. Participating women of fertile age must have no current pregnancy, which will be assessed by pregnancy test.
- Body mass index 27-45 kg/m^2

##### **Exclusion criteria**

- Diagnosed with diabetes mellitus according to the WHO criteria
- Anti-diabetic medication
- Active liver disease

- At screening or at any subsequent visit a level of aspartate aminotransferase (ASAT) or alanine aminotransferase (ALAT) of more than three times the upper limit of the normal range
- Gastrointestinal ailments which may interfere with the ability to adequately absorb sulforaphane
- At screening visit creatinine > 130 µmol/L
- Coagulation disorder or current anti-coagulant therapy, which may be affected by the BSE
- Diagnosed with a cardiovascular disease or known cardiovascular event, transient ischemic attack, coronary by-pass surgery or other coronary vessel intervention within 6 months prior to enrolment
- Systemic glucocorticoid treatment
- Herbal treatment, defined as food supplement (except multivitamin treatment) with herbal or vegetable extracts that may affect blood glucose
- Allergy to broccoli
- Participant unable to understand the study information
- Participation in other clinical trial which may affect the outcome of the present study
- Any other physical or psychiatric condition or treatment that in the judgment of the investigator makes it difficult to participate in the study.

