- Venous fasting blood samples are drawn for analysis of glucose, creatinine, ASAT, ALAT, GT, ALP, bilirubin, PK, thrombocytes. Total blood volume is estimated to 25 mL.
- If venous fasting blood glucose is above or equal to 6.1 mmol/l and below 7.0 mmol/l, the participant is scheduled for visit 2, which will be 1-14 days after

the screening visit.

- They receive a tube for stool sampling and are instructed how to sample.

### 3.4 Visit 2

Participants who are eligible to participate will be scheduled for a second visit 1-14 days after their first visit. If the venous analyses from the screening visit of creatinine, ASAT, ALAT, GT, ALP, bilirubin, PK, thrombocytes, show clinically relevant abnormalities that upon decision by PI precludes participation, that the subject's visit 2 will be cancelled.

The participants are recommended not to conduct intense physical activity or drink alcohol 24 h before the visit. They should be fasting since midnight. Nicotine users should not have used nicotine the same day.

The following will be done at visit 2:

- ID is checked
- Information on current use of pharmaceutical drugs is collected
- Venous fasting blood samples are drawn for analysis of fasting glucose, HbA1c, insulin, c-peptide, Hb, GT, lipid levels (HDL, LDL, total cholesterol, triglycerides), TSH and free fatty acids. Total blood volume is estimated to 25 mL.

If venous fasting blood glucose is 6.1-6.9 mM the individual can be included in the study and we proceed with the following:

- For women of fertile age we make a pregnancy test and proceed with the remaining points only if that is negative.
- The participant receives a study ID, using consecutive numbers and are randomized to receive BSE or placebo (see point 5.3 Randomization)
- Length, weight, and waist-hip circumference are measured.
- Participants complete a questionnaire on dietary habits, physical activity, smoking and alcohol habits.
- Participants leave their stool sample
- A note is made in the medical record about the visit.
- Study subjects receive their study medication (BSE or placebo) to bring home
- They receive a tube for stool sample to be sampled before visit 3

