- Scheduled for visit 3. Visit 3 should be scheduled on the same weekday as visit 2, 12 (ideally) or 13 weeks later. If that is not possible, e.g. because of public holidays or unavailability of the participant to come on an assigned day, visit 3 will be scheduled as soon as possible 12 weeks after visit 2. Latest possible date for visit 3 is 14-15 weeks after visit 2. If that is not possible to manage for the participant, he or she have to be excluded. The participant is instructed to contact us as soon as possible if he or she needs to change date for visit 3.

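### The ASAT/ALAT limit applies at every visit after screening, but both enzymes are planned at screening only, so the later part of the rule has no planned data

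*Protocol*

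**What the plan says.** The exclusion criteria in Protocol section 3.2 include this limit, a multiple of the upper normal limit: "At screening or at any subsequent visit a level of aspartate aminotransferase (ASAT) or alanine aminotransferase (ALAT) of more than three times". In the same list, the renal criterion is confined to one visit, beginning "At screening visit creatinine". The withdrawal criteria that follow say that a participant who develops an excluded condition during the study is to be withdrawn.

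The blood panels are set out visit by visit:

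- **Screening (3.3):** "Venous fasting blood samples are drawn for analysis of glucose, creatinine, ASAT, ALAT, GT, ALP, bilirubin, PK, thrombocytes".
- **Visit 2 (3.4):** "Venous fasting blood samples are drawn for analysis of fasting glucose, HbA1c, insulin, c-peptide, Hb, GT, lipid levels", followed by TSH and free fatty acids. ASAT and ALAT are absent.
- **Between visits (3.6):** one telephone contact, 2 to 4 weeks into treatment. No blood is drawn.
- **Visit 3 (3.7):** the same analytes as visit 2, again without ASAT or ALAT.

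On timing, section 3.4 states: "Participants who are eligible to participate will be scheduled for a second visit 1-14 days after their first visit". Randomization and dispensing take place at visit 2: "Study subjects receive their study medication (BSE or placebo) to bring home". The end of the window is also fixed there: "Latest possible date for visit 3 is 14-15 weeks after visit 2".

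**The concern.** The exclusion list separates a screening-only criterion (creatinine) from a continuing one (ASAT/ALAT), and the withdrawal criteria give the continuing one force. The schedule then supplies no ASAT or ALAT value after screening. Two provisions of the same document do not fit together.

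What is at stake is liver safety information, not efficacy. Section 7.1 describes a 7-day safety study in 12 healthy volunteers. ALT went above the upper limit of normal in 2 of them, both on BSE, and AST went above normal in 2 of 12. This trial gives BSE daily for 12 weeks, and for up to 15 if visit 3 is postponed. As planned, it ends with no ASAT or ALAT value in either arm after dosing, although blood is drawn at visit 3 anyway. The same section reports TSH rises, and TSH is measured at visits 2 and 3.

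**Working it through.** The plan gives no figure to reproduce. The check sets the rule against the schedule.

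**Coverage**

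| Occasion | Blood drawn | Rule applies (3.2) | ASAT/ALAT planned |
|---|---|---|---|
| Screening (3.3) | yes | yes | yes |
| Visit 2 (3.4) | yes | yes | no |
| Telephone contact (3.6) | no | – | no |
| Visit 3 (3.7) | yes | yes | no |

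- Blood-sampling visits covered by the rule: 3.
- With ASAT/ALAT planned: 1 of 3.
- After screening: 0 of 2.

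GT is measured at visits 2 and 3 but cannot stand in. It is a different enzyme, it feeds the fatty liver index (4.3), and the protocol sets no limit for it.

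**Age of the last planned value at visit 3**

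The formula is days from screening to visit 2, plus weeks from visit 2 to visit 3 times 7. The inputs are 1 to 14 days and 12 to 15 weeks (3.4).

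- Shortest: 1 + 12 × 7 = 85 days.
- Longest: 14 + 15 × 7 = 119 days.

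**When a planned result could act**

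Visit 2 comes before the first dose and visit 3 ends treatment. With both assays added at both visits, no scheduled result would arise during dosing. A visit 3 value therefore serves end-of-treatment follow-up.

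**Volume of added results**

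The formula is assays × visits × participants, with 100 participants (3.9).

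- Visit 3 only: 2 × 1 × 100 = 200.
- Visits 2 and 3: 2 × 2 × 100 = 400.

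Both are upper figures. They assume no dropout, and that the visit 2 assays are run only for those randomized. If only the 37 per group that section 6.1 requires reach visit 3, that visit gives 2 × 74 = 148 results.

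**The case against.** The strongest reply is that little depends on this. The primary outcome, the sample size and the stated objectives are untouched. ASAT and ALAT are not effect variables, and one phrase could be deleted to make the text consistent. Section 7.1 adds that ALT rose in all subjects of the volunteer study, placebo included, and finds no clinically significant effect. Section 8.1 reports no severe changes in routine analytes. This stands as an argument on severity. It does not remove the mismatch.

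Deleting the phrase is the weaker cure. The rule is not restricted to scheduled visits, so a value above the limit from an unscheduled or outside test would now support withdrawal. Confining the criterion to screening would remove that numeric trigger for up to 15 weeks of dosing. Active liver disease, the investigator's judgment and withdrawal for related serious adverse events would be what remains.

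A reader might infer three stronger things, which the document does not support:

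- **That a stopping rule has been lost.** No scheduled blood sample falls during dosing, so the listed visits could not have stopped treatment early even with the assays.
- **That the rule is inoperative, or that the site cannot show it was followed.** The rule depends on an observed value. Without one there is no known breach to document, and unscheduled results can still trigger it.
- **That re-screening requires a second ASAT/ALAT test.** Section 3.1 says "the person has to pass the study criteria at both the new screening visit and visit 2 to be randomized", but it concerns people who failed because fasting glucose varies. The gates listed at visit 2 are glucose and, for women of fertile age, a pregnancy test. The screening liver values, 1 to 14 days old, are reviewed beforehand and can cancel the visit.

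**Conclusion.** The inconsistency is real and minor. The ASAT/ALAT limit is written to continue after screening and is backed by withdrawal, but planned data exist at 1 of 3 blood-sampling visits and at 0 of the 2 after screening. The accurate statement is that the post-screening part has no planned data.

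This rests on reading the visit 2 and visit 3 panels as complete lists, which is how they are written. Section 8.1 mentions liver status in general terms but ties it to no visit. The conclusion does not depend on BSE harming the liver. The volunteer figures are small, and they show only why an end-of-treatment value is worth having. It is best treated as a cheap improvement.

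**What to change.** 1. **Keep the post-screening limit, and say what it acts on.** Word it to apply to any ASAT or ALAT result that becomes available during treatment, including unscheduled tests.
2. **Add ASAT and ALAT to the visit 3 panel.** Follow up raised values as adverse events under section 7.2. State that a raised visit 3 value does not remove that participant's visit 3 data from the ITT analysis. The compliance rule in 6.1 is a separate matter.
3. **Optionally add both at visit 2** as a pre-dose baseline. Do not make them a condition for dispensing: kits are handed out at that visit, routine samples go to the central laboratory (6.3), and no turnaround time is given for these assays.

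The cost is at most about 200 routine results, or 400 with visit 2, on blood already being drawn, plus follow-up of raised values. No visit or needle is added. A true on-treatment stopping check would need a mid-treatment sample, and so an extra visit. That is for the sponsor's clinicians to decide and is not proposed here.
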